## Exclusion criteria

- Patients treated with albendazole during the 4 previous weeks
- Known intolerance or allergy to any study drug
- Viral hepatitis (HBV, HCV) or other known active liver disease
- HIV or other known immunosuppressive condition
- History of epilepsy, encephalitis, meningitis or encephalopathy
- Any other acute or chronic medical condition, medication or psychosocial factor(s) deemed by the Investigator to put the potential participant at greater than acceptable risk or to significantly affect study outcomes
- Pregnancy, no breastfeeding and no agree to use a contraceptive method for women with childbearing potential

## Recruitment & informed consent

Adult male subjects in the BuDiLoLo study found to be harbouring *L. loa* microfilariaemia < 50,000 mf/mL will be approached by study team with regards to possible participation in the trial. The aims, design, in- & exclusion criteria and procedures of the trial will be provided to them in written form as well as explained to them in understandable terms and they will be given adequate time (≥2 days) to consider.

If following this period they are still interested in participating, potential participants will be invited for a screening visit where they will first be asked to sign a written informed consent form. In the case of illiterate participants, an impartial witness will be asked to co-sign the consent form.

## Withdrawal of participants

Participants may be withdrawn from the study prior to completion of follow-up, under the following circumstances:

- On direct request of the participant; the participant need not provide any reason for withdrawal
- If in the opinion of investigator(s), safety monitor and/or supervising ethical committee continued participation poses unacceptable risks to one or more subjects

If further follow-up of withdrawn participants is considered important for purely safety purposes, the participant(s) will be informed of this and of the risks of loss to follow-up will be clearly explained to them.

# Procedures

## Study schedules

Arms 1+2 will commence simultaneously; after arms 1+2 have started, arms 3+4 will also start in parallel. Basic follow-up schedules will be similar for subjects in all 4 arms: visits will take place at screening, immediately prior to commencement of the study arm and thereafter daily for the first week, twice per week for the subsequent two weeks (i.e. until the end of the first albendazole course in arms 2-4) and thereafter once per week until the second course of treatment commences in arms 3+4. This second round of treatment will commence as soon as 90% of the subjects still in follow-up in arm 4 drop below the threshold of 4000 mf/mL. A similar visit schedule will then be used for the second treatment round in arms 3+4 (daily during the first week of treatment and twice per week during the second week). Thereafter, twice monthly follow up visits will be scheduled for the remaining follow-up period until the end of follow-up at 6 months.

### Arm 1

No anti-helminthic medication will be used, although symptomatic treatment may be provided if deemed clinically appropriate. Participants will be seen at screening, immediately prior to commencement of the study arm and thereafter daily for the first week, twice per week for the subsequent two weeks and thereafter once per week until eight weeks after start of the study arm and then twice monthly until the end of follow-up at 6 months. At the end of the study, any participants in this arm who wish to, will be provided with a 3-week course of albendazole (400mg/day), in line with Gabonese national guidelines for MDA in Loa-endemic populations. Note that no further follow-up will be performed during this treatment course.

### Arm 2

A single 3-week course of albendazole (800mg/day) will be provided at commencement of the study arm, simultaneously with the start of Arm 1. Participants will be seen at screening, immediately prior to commencement of the study arm and thereafter daily for the first week, twice per week for the subsequent two weeks (until the end of the albendazole course) and thereafter once per week until eight weeks after start of the study arm and then twice monthly until the end of follow-up at 6 months.

### Arm 3

A single 3-week course of albendazole (800mg/day) will be provided at commencement of the study arm, simultaneously with the start of Arm 4. Participants will be seen at screening, immediately prior to commencement of the study arm and thereafter daily for the first week, twice per week for the subsequent two weeks (i.e. until the end of first albendazole course) and thereafter once per week until 90% of the subjects still in follow-up in arm 4 drop below the threshold of 4000 mf/mL; if this criterion is not yet achieved by week 8, subsequent visits will be reduced to twice monthly. All participants will then be re-treated with a 2-week course of albendazole (800mg/day). All subjects will be seen daily for follow-up visits during the first week of re-treatment and twice per week during the second week. Thereafter further follow-up visits will take place twice monthly until the end of follow-up at 6 months.

### Arm 4

A single 3-week course of albendazole (800mg/day) will be provided at commencement of the study arm, simultaneously with the start of Arm 3. Participants will be seen at screening, immediately prior to commencement of the study arm and thereafter daily for the first week, twice per week for the subsequent two weeks (i.e. until the end of first albendazole course) and thereafter once per week until 90% of the subjects still in follow-up in arm 4 drop below the threshold of 4000 mf/mL; if this criterion is not yet achieved by week 8, subsequent visits will be reduced to twice monthly. All participants with <4000 mf/mL will then be treated with a single dose of ivermectin; any subjects *not* achieving <4000 mf/mL at this time point will instead commence continuous re-treatment with *albendazole* until microfilaraemia becomes undetectable, until treatment is no longer tolerated, or until the end of follow-up (whichever occurs first). *All* subjects will be seen daily for follow-up visits during the first week following ivermectin/albendazole (re-)treatment and twice per week during the second week. Thereafter further follow-up visits will take place twice monthly until the end of follow-up at 6 months.

## Study visits

### Screening

Potential participants will be informed again about the study aims, design, in- & exclusion criteria and procedures. If still willing to participate, subjects will be asked to sign written informed consent. Thereafter, a full medical history and concomitant medication will be recorded and a physical examination will be performed. Blood will be drawn for laboratory safety parameters (haematology, biochemistry, serology) and to confirm microfilarial levels and to exclude pregnancy in female subjects. In addition a single stool sample and urine sample will be collected to assess
helminth infection (since we will be treating with albendazole which
will also have an effect on many helminths), which could affect
tolerability and influence non-specific symptoms such as pruritus. Indeed helminth infection also affect immune response, therefore it will be necessary to know the subject helminth status.

Any abnormal findings that result in exclusion from the study and/or require treatment will be communicated to the subject; for any treatment required beyond that which can be provided directly by the study team, subjects will be referred to other healthcare providers as appropriate.

### Randomisation and start of study arms

Once sufficient participants are included for the entire study, participants will be randomized to one of the four study arms. The generation of the randomization sequence will be computer assisted with a block size of 10 with a fixed allocation of 12 patients for each treatment arm and 6 for the control group. The randomisation list will be produced by a team independent of the investigators and will be provided as sealed opaque envelopes to the study team. The investigator may only open the sealed opaque envelope after informed consent has been obtained and the subject is to be allocated to a treatment arm. Treatment allocation will then be revealed to the subject. No change of treatment allocation will be permitted in the course of this trial. If it is in the interest of the patient safety, the patient will be removed from the study and will receive appropriate routine care. In case of requirement of allocation of extra-patients to a study arm due to excessive loss-to-follow-up, patients will be screened and will be allocated to the respective treatment arm without randomization. This fact will be clearly acknowledged in the analysis and presentation of the data.

At the first visit of their study arm (DT0), each participant will again have blood drawn for laboratory safety parameters (haematology and biochemistry) and for quantification of *L. loa* microfilaraemia. In addition, blood may be collected for immunology (baseline). Participants in arms 2, 3 & 4 will receive their first dose of albendazole under supervision.

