## Study size

This study is a descriptive study and is not powered for statistical testing of a predefined hypothesis. As a proof of principle study, this trial aims to describe the crude effect of respective treatment regimens on the proportion of subjects achieving sustained reduction in peripheral microfilaraemia and on the kinetics of parasitaemia. For this purpose a total of 8 evaluable subjects per treatment arm is required at the end of 6-months’ follow-up. In order to allowing for up to ⅓ (33%) loss to follow-up during this period, 12 patients will be recruited into each treatment group. An additional 6 patients will be recruited for the control group for the description of the natural variability of microfilaraemia. Thus the total study size will be 42 participants: n=6 in study arm 1 and n=12 each in arms 2-4. In case of drop out of more than 33% in any study arm for evaluation of the primary endpoint, further patients will be screened and included in the respective study arm to achieve at least 8 evaluable patients in each treatment group.

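### Top-up of a depleted arm with non-randomised patients, and removal of safety cases from the study, mean that the month-6 proportion may no longer describe the randomised arm

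*Protocol*

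**What the plan says.** Section 5.2 (Study size) describes the trial without a formal test: "This study is a descriptive study and is not powered for statistical testing of a predefined hypothesis". The size rests on a target instead: "a total of 8 evaluable subjects per treatment arm is required at the end of 6-months’ follow-up". With an allowance of up to one third lost to follow-up, each treatment arm recruits 12, and 6 controls are added.

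Two rules then deal with participants who leave.

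- **Replacement.** Once an arm has lost over a third of its participants for the primary endpoint, section 5.2 says that "further patients will be screened and included in the respective study arm to achieve at least 8 evaluable patients in each treatment group". Section 6.2.1 (Randomisation and start of study arms) adds that these "patients will be screened and will be allocated to the respective treatment arm without randomization", and promises that this will be made clear when the data are analysed and presented.
- **Removal.** Section 6.2.1 rules out any change of allocated treatment and says that, where patient safety calls for it, "the patient will be removed from the study and will receive appropriate routine care". Section 5.6 (Withdrawal of participants) mentions follow-up of those who have left only where it matters for safety.

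The primary efficacy endpoint (section 4.3.1) is the proportion below 100 mf/mL at 6 months. Section 9.1 refers the analysis to a predefined statistical analysis plan, which is not at hand.

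**The concern.** Both rules act on who contributes a month-6 count, and both act after randomisation.

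Replacement depends on whether outcomes are available in a given arm. The added patients enter later than those they stand in for, and their arm is already decided. They were never part of the random split, yet section 5.2 counts them inside the arm towards its 8 evaluable patients. Removal can take away the month-6 count for a reason connected with treatment, because a safety problem ends study participation and not merely study drug. If those who leave differ in response from those who stay, the proportion among the evaluable differs from the proportion among the randomised.

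No type I error or power is at stake, since nothing is tested. The proportions themselves are the product of the trial. Section 4 says the pilot is to identify regimens for adequately powered comparative trials, section 4.2 sets out to evaluate and compare the regimens, and section 4.1 calls the design randomised and controlled. A regimen could be carried forward or dropped on a figure that mixes randomised and assigned patients.

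**Working it through.** **1. The plan's own figure.** Inputs from section 5.2: 8 evaluable per treatment arm, loss up to 1/3.

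8 / (1 − 1/3) = 12 per treatment arm; 6 + 3 × 12 = 42. Both figures reproduce. Nothing here changes the sample size.

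**2. When replacement starts.** With 4 of 12 lost (one third), 8 remain and nothing needs adding. The rule first bites at 5 of 12 lost, when 7 remain and 1 is added.

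**3. How often that happens.** Let X be the number lost of 12 and d the true loss rate, which the protocol does not predict and is assumed here. Losses are taken as independent between participants and between arms.

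P(X ≥ 5) = 1 − Σ(k = 0 to 4) C(12, k) d^k (1 − d)^(12 − k) = q; at least one of three treatment arms: 1 − (1 − q)³.

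| Assumed loss d | One arm, q | At least one of three |
|---|---|---|
| 10% | 0.004 | 0.013 |
| 20% | 0.073 | 0.202 |
| 25% | 0.158 | 0.402 |
| 1/3 (upper allowance) | 0.368 | 0.748 |

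**4. What it can do to the proportion.** Illustrative counts, not taken from the protocol: 5 of 12 lost, 2 responders among the 7 retained, 1 patient added.

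| Basis | Proportion |
|---|---|
| All 12 randomised, missing counted as not reached | 2/12 = 17% |
| Completers only | 2/7 = 29% |
| Topped up, added patient does not respond | 2/8 = 25% |
| Topped up, added patient responds | 3/8 = 38% |
| All 12 randomised, missing counted as reached | (2 + 5)/12 = 7/12 = 58% |

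The randomised arm lies somewhere between 17% and 58%. Both topped-up figures fall inside that range, so the error may be upward or downward. Relative to completers, one addition moves the figure down to 25% or up to 38%.

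**5. The follow-up passages side by side.**

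- Section 6.2.1 takes a safety case out of the study.
- Section 5.6 foresees follow-up after withdrawal for safety only, and mentions no microfilaria counts for efficacy.
- Section 6.1.4 (Arm 4) lets continuous albendazole end for intolerance, yet schedules visits for all subjects to month 6. Stopping drug and leaving the study are separate there.
- Section 7.6 collects serious adverse events from all participants to the end of follow-up. The primary safety endpoint in section 4.3.2 also includes non-serious grade 3 events, which section 7.6 does not cover after removal.

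These four places do not give one answer on what is collected after a safety removal.

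**The case against.** The strongest reply is that analysis sets, handling of missing outcomes and display of added patients normally belong in the statistical analysis plan, and one is announced. That stands as far as it goes: the protocol nowhere says that added patients are pooled with randomised ones, or that lost participants leave the denominator. It does not answer the conduct rules. No analysis plan can recover counts that were never collected or randomise patients who were simply assigned, and section 5.2 already places the additions inside the arm for its target of 8.

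Further points that stand:

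- Replacement is conditional. Losses of up to 4 of 12 are not replaced.
- Section 6.2.1 promises acknowledgement in the analysis as well as in the presentation.
- One third is an upper allowance, so 37% and 75% are ceiling scenarios.
- In the illustration, the move from 17% to 29% (2/7 − 2/12 = 12 points) comes from the denominator. The top-up adds 9 points (3/8 − 2/7), and only if the added patient responds.
- The removal sentence follows directly on the ban on changing allocation and may be meant for patients who need other care, not for everyone who stops study drug.

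A reader might also infer that replacements enter six months or more after the others, or that they are chosen for a good prognosis. Neither is in the text. A fifth loss could trigger a top-up well before month 6. Additional patients are screened, and no exemption from the eligibility criteria is stated. Being told the arm is not peculiar to them either, because the trial is open-label.

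**Conclusion.** The point holds in conditional form. Followed exactly, the protocol adds non-randomised patients to any treatment arm with at least 5 of 12 lost, and it may lose month-6 counts for reasons connected with treatment. In that event the reported proportion may no longer describe the randomised arm, and disclosure does not repair it.

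The chance of a top-up in at least one treatment arm runs from 1% at 10% loss to 75% at the protocol's upper allowance, under the assumed loss rates and independence. In the illustration, the randomised arm is known only to lie between 17% and 58%, while the topped-up figure is 25% or 38%.

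It is tempting to conclude that the rules inflate efficacy precisely where tolerability is worst. The documents do not support that. They give no cause for losses, do not show that those lost are failures, partly keep participants in follow-up (sections 6.1.4 and 7.6), and do not fix a pooled or evaluable-only denominator. The direction of the bias is open. As the trial is a descriptive pilot, the consequence is a less interpretable estimate for choosing regimens, not an invalid test.

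**What to change.** 1. In sections 5.2 and 6.2.1, state that patients added without randomisation are shown in a separate row and are not pooled into the randomised arm's primary proportion. State that this proportion is reported on all randomised participants in the arm, with a missing month-6 count taken as not reaching the threshold, and with a completers-only result as sensitivity analysis. Mirror this in the statistical analysis plan.
2. Reconcile the removal sentence in section 6.2.1 with sections 5.6, 6.1.4 and 7.6. Make clear that participants who stop study treatment still have microfilaria counts and adverse events collected to month 6, with their consent and where those overseeing safety under section 5.6 do not object. This concerns data collection only. When treatment should stop remains a clinical matter for the protocol's authors.

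The total stays at 42. The cost is wording in the protocol and analysis plan, follow-up visits for the few participants affected, and response proportions that will look somewhat less favourable.

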### Visits during intake of albendazole

Once daily visits will be performed during the first week of all study arms, including observed intake of one daily dose of albendazole in arms 2-4 and recording of AEs in all. For the two weeks thereafter, visits will be performed twice weekly. Patients will be specifically and repeatedly advised that albendazole intake shall follow intake of a standard meal as this importantly enhances the bioavailability of albendazole. Note that intake of albendazole on non-visit days and the intake of the *second* dose on visit days will not be supervised. Blood samples will be drawn for laboratory safety parameters (haematology and biochemistry) and quantification of microfilaraemia on the 1^st^ day after start of treatment (DT+1), DT+3, DT+7, DT+10, DT+14, DT+17 and DT+21. In arm 1, blood samples will be drawn for the quantification of microfilaraemia according to a similar schedule. At DT+14 additional blood may be collected for immunology in all study arms. (*Visit designations are approximate and may vary by ±1 day in the first week after start of treatment and by ±2 days in the two weeks thereafter.*).

If clinically indicated a physical examination and/or additional blood draw(s) for laboratory safety parameters will be performed.

Subjects in arm 3 (and subjects in arm 4 who failed to achieve <4000 mf/mL) will undergo a similar schedule of visits during their second course of albendazole, commencing on the first day of re-treatment (DRT0) except that these visits will last only until DRT+14, instead of DRT+21. Additional blood may be collected for immunology at DRT0 and DRT+14. (*Visit designations are approximate and may vary by ±1 day in the first week after start of treatment and by ±2 days in the week thereafter.*)

### Visits following intake of ivermectin

Subjects in arm 4 who achieve <4,000 mf/mL will receive a single dose of ivermectin under observation, followed by daily visits to record AEs during the first week after intake and twice weekly in the second week. Blood will be drawn for laboratory safety parameters (haematology and biochemistry) and quantification of microfilaraemia on the day of treatment (DRT0), DRT+1, DRT+3, DRT+7, DRT10 and DRT+14. Additional blood may be collected for immunology at DRT0, DRT+1 and DRT+14. (*Visit designations are approximate and may vary by ±1 day in the first week after start of treatment and by ±2 days in the week thereafter.*)

If clinically indicated a physical examination and/or additional blood draw(s) for laboratory safety parameters will be performed.

### Follow-up visits

In arms 1+2, weekly follow-up visits will take place from week 4 through week 8; thereafter, twice monthly visits will take place until the end of follow-up (at month 6). In arms 3+4 weekly follow-up visits will take place between the first and second courses of treatment; if re-treatment has not started by week 8, then these visits will be reduced to twice monthly. Twice monthly visits will also take place from two weeks after commencement re-treatment until the end of follow-up (at month 6) in arms 3+4. AEs will be recorded and blood drawn for quantification of microfilaraemia at each visit. Additional blood may be collected for immunology and laboratory safety parameters at the end of follow-up (at month 6) in all study arms. If clinically indicated a physical examination and/or additional blood draw(s) for laboratory safety parameters will be performed. At day 28, day 63 and at 6 months an additional pregnancy test will be performed in female subjects.

The investigator will collect pregnancy information on female participant who becomes pregnant during drug intake or three months after the last dose of study drug. The participant will be follow up to delivery and the neonate information will also be collected. Any termination of pregnancy will be reported.

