| V3(08-06-2018) | Allow inclusion of female (in additional to male) subjects. In fact the original reason to exclude women from the study was justified by the concern that women could get pregnant during the course of study, knowing that albendazole is contraindicated during pregnancy. However, the screening results from BuDiLoLo show that almost all women with high *Loa loa* parasitemia are beyond child bearing age.  -Clarify that analysis of biological safety parameters will be performed at the end of follow-up without any clinical indication.  -Clarify that Saponin method will be used to quantify Loa Loa microfilareamia only in sample that are tick smear will negative | [name] |
|  |  |  |
|  |  |  |

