**Table 1. Summary of drugs available for the treatment of *L. loa***

|  | **Regimen** | **Macrofilaricidal effect** | **Microfilaricidal effect** | **Adverse Effects** | **Contraindications** | **Comment** |
| --- | --- | --- | --- | --- | --- | --- |
| diethylcarbamazine | 10mg/kg in three divided doses for 21 days | yes | yes (direct?) | Mazotti reaction, encephalopathy in high microfilaraemia (>2500 mf/µl) | cardiac or renal impairment | Drug of choice for curative treatment with sub-optimal efficacy and problematic safety |
| ivermectin | 150µg/kg-400µg/kg single dose | no | yes (direct) | Mazotti reaction in oncho-cerciasis; encephalopathy in patients with high *L. loa* microfilaraemic loads | high *L. loa* microfilaraemia | Not useful for curative treatment of loiasis but potentially for control of transmission |
| albendazole | 200mg qd to 400mg bid for varying duration | yes | no (only indirect reduction) | minor | pregnancy | Safe drug with potential use for curative treatment and control of transmission |

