## Timeframe

The trial is set to start including participants as soon as ethical clearance is obtained (e.g. by October 2017), since the underlying BuDiLoLo study has already started screening subjects. The recruitment phase ends once sufficient participants (n=42) are included for the overall design of the trial. The duration of the recruitment phase thus depends partially on the screening rate in BuDiLoLo, but is anticipated not to exceed ~2 months. Arms 1 and 2 of the trial will commence as soon as recruitment is completed and randomization is performed. Arms 3 and 4 will commence in parallel thereafter. Follow-up in each study arm will last 6 months. Thus the total duration of the trial is anticipated to be ~9-10 months.

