## Inclusion criteria

- Adult, participants of either sex
- *L. loa* microfilaria < 50,000 mf/mL
- Intention to remain residing in study area and comply with study procedures throughout 6 month follow-up period
- Signed written informed consent

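### Pregnancy testing is not tied to albendazole dosing: no test is required on the first day of the first course or of re-treatment

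*Protocol*

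**What the plan says.** The Document history entry for version 3 explains that women were first excluded over possible pregnancy, "knowing that albendazole is contraindicated during pregnancy". Table 1 also lists pregnancy as the contraindication for albendazole. Women are now eligible: section 5.3 reads "Adult, participants of either sex", with an upper but no lower limit on microfilaraemia.

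Pregnancy tests are set in two places. The screening blood draw (section 6.2.1, Screening) is used to exclude pregnancy. Section 6.2.4 then adds: "At day 28, day 63 and at 6 months an additional pregnancy test will be performed in female subjects".

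No dosing visit includes one:
- At DT0 (section 6.2.1, Randomisation and start of study arms), blood is taken for haematology, biochemistry, the microfilarial count and optionally immunology.
- The visit lists for the second albendazole course (6.2.2) and for ivermectin (6.2.3) name no pregnancy test at DRT0.
- The safety panel in 6.4.2 contains none.

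On timing, section 4.4 says that recruitment "is anticipated not to exceed ~2 months", that arms 1 and 2 start once it is complete, and that "Arms 3 and 4 will commence in parallel thereafter". Section 6.1 starts the second round "as soon as 90% of the subjects still in follow-up in arm 4 drop below the threshold of 4000 mf/mL". All of arm 3 then receives albendazole again. Anyone in arm 4 not below 4000 mf/mL takes it continuously, possibly to the end of follow-up (6.1.4).

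**The concern.** A pregnancy test protects against a contraindicated drug only if it is read before that drug is given. Here the tests follow the calendar and the dosing follows other events: completion of recruitment for the first course, and the arm 4 response for the second. Followed exactly, the plan can start or restart albendazole in a woman of childbearing potential on an out-of-date result. Fetal exposure cannot be undone once it has happened.

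The version 3 rationale does not close the gap. It says that almost all women with high parasitaemia are past childbearing age, whereas the current criterion also admits women with lower loads, about whom the protocol says nothing. This matters most at DT0 and in arm 3, where albendazole is given whatever the count. It matters less for an arm 4 participant on continuous albendazole, who is by definition still at or above 4000 mf/mL.

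**Working it through.** Days are counted from the start of the participant's arm. Treated participants: 3 × 12 = 36 of the planned 42 (section 5.2).

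**1. First course.** It runs to day 21 and the first test after screening is at day 28: 28 − 21 = 7 days after the course ends. No scheduled test can prevent or interrupt exposure during this course.

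**2. Age of the screening result at DT0.**
- Arm 2: the wait is at most the length of recruitment, about 2 months for the first woman screened. If screening is spread evenly (an assumption), the average is 2 / 2 = 1 month.
- Arms 3 and 4: the wait is longer by a stagger that the protocol does not state. Section 4.4 gives a total of about 9–10 months. If everything beyond recruitment and follow-up were stagger, it would be 9 − 2 − 6 = 1 to 10 − 2 − 6 = 2 months, making the oldest result 3–4 months old. This is an inference from approximate durations.

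**3. Age of the last scheduled test at DRT0.** The day is not fixed, and section 6.2.4 allows for it to fall after week 8.

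| DRT0 | Last test | Age |
| --- | --- | --- |
| before day 28 | screening | not fixed by the plan |
| day 35 | day 28 | 35 − 28 = 7 days |
| day 62 | day 28 | 62 − 28 = 34 days |
| day 91 | day 63 | 91 − 63 = 28 days |
| day 119 | day 63 | 119 − 63 = 56 days |
| day 162 | day 63 | 162 − 63 = 99 days |

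These are illustrative days; the protocol gives no expected date for DRT0.

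**4. How many can be on continuous albendazole.** The 90% rule limits this.
- One participant not below 4000 mf/mL is compatible with 11/12 = 91.7%, 10/11 = 90.9% and 9/10 = 90.0%.
- Two are not: 10/12 = 83.3% and 9/11 = 81.8%.
- With 9 or 8 in follow-up even one is too many: 8/9 = 88.9% and 7/8 = 87.5%.

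So at most one participant is affected when 10–12 remain, and none when 8 or 9 remain. Section 4.1 asks for more than 90%, under which 9/10 also fails.

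**5. Untested time on continuous albendazole.** No test is scheduled between day 63 and month 6 (taken as day 182; calendar range 181–184).
- Start by day 63: 182 − 63 = 119 days = 17 weeks (range 118–121 days).
- Start day 70: 112 days = 16 weeks.
- Start day 84: 98 days = 14 weeks.
- Start day 112: 70 days = 10 weeks.

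**6. With tests tied to dosing.** The result is 0 days old at the start of each albendazole course. Tests at days 91, 119 and 147 reduce the longest gap during continuous albendazole to 182 − 147 = 35 days.

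**The case against.** The sentence in 6.2.4 is not wrong in itself: it schedules follow-up tests and does not claim to clear anyone for dosing. The plan also has several safeguards. Pregnancy is an exclusion, contraception is intended for women of childbearing potential, screening includes a test, three later tests follow, participants can be removed for safety, and pregnancies are followed to delivery. Exposure would require conception despite agreed contraception, between the last test and dosing. Few such women may enrol, and the protocol gives no number. The 2-month figure is an expectation about recruitment, not a cap, and describes arm 2 only. The DRT0 gap is less certain than the DT0 gap, because weekly visits after the first course make it plausible that the day 28 test comes first. The continuous-albendazole case concerns at most one person.

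Most of this stands as a limit on size. None of it puts a test at DT0. Agreement to contraception does not replace a test, and the criterion in 5.4 is so garbled that its meaning has to be guessed. Pregnancy follow-up acts only after exposure. The extra draws allowed when clinically indicated are for safety parameters, and the panel in 6.4.2 has no pregnancy test. Nor does the protocol show that a result can be had on the dosing day, which the fix must settle.

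**Conclusion.** The point holds. The plan requires no pregnancy test at the start of either albendazole course, although it calls the drug contraindicated in pregnancy.

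The DT0 gap is the firmest part: a result up to about 2 months old in arm 2, older in arms 3 and 4, and no further test until a week after the course. The DRT0 gap ranges from days to several weeks or more, depending on the arm 4 response. The 17-week interval is a maximum for at most one participant, who would also have to be a woman of childbearing potential, start by day 63 and continue to month 6.

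The sizes rest on the stated recruitment expectation, on days counted from the start of each arm, and on month 6 as day 182. The number of women at risk cannot be estimated from the protocol. This is a participant-safety point that should be corrected; it does not touch the endpoints, the sample size or the analysis.

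**What to change.** For women of childbearing potential, require a negative pregnancy test with the result known before that day's dose:
- at DT0 in arms 2–4;
- at DRT0 before any albendazole re-treatment, meaning arm 3 and any arm 4 participant not below 4000 mf/mL;
- about monthly during continuous albendazole, for example at days 91, 119 and 147, between the planned day 63 and month 6 tests.

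If a test is positive, give no albendazole, and apply the existing safety-removal rule (6.2.1, Randomisation and start of study arms) and the pregnancy follow-up in 6.2.4. The first dose at DT0 is already supervised, so it can be held until the result is read.

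Cost: one extra test per woman in arm 2 and per ivermectin recipient in arm 4, two in arm 3, and up to five (1 + 1 + 3) for the one possible participant on continuous albendazole. Even if all 36 treated participants were women of childbearing potential, the total would be 36 (DT0) + 12 (arm 3 DRT0) + 1 (arm 4 albendazole DRT0) + 3 (monthly) = 52 tests. The real number would be far lower. The tests use planned visits and blood draws.

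Two wording edits belong in the same amendment. In 5.4, the breastfeeding item should exclude women who breastfeed (the clinical team should confirm), and the contraception clause should be made readable. In 4.1 and 5.5, the descriptions still limited to men should cover both sexes.
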